## Abstract

**Background::**

Despite introducing novel analgesics, pain management for spine surgery remains a challenge. Multimodal pain control has recently gained popularity in surgical spine care. We proposed a novel management approach using multimodal cocktail analgesics. Injection to skin surrounding surgical incision site will be given perioperatively. This study evaluates the safety and efficacy of cocktail analgesic injection on pain management following lumbar spinal fusion surgery.

**Methods::**

Thirty-six patients with degenerative lumbar spinal diseases on the waiting list for lumbar spinal fusion surgery will be recruited. Patients will be randomly assigned to receive either cocktail analgesic injection or sterile saline before surgical wound closure. All patients will routinely receive postoperative intravenous patient-controlled analgesia (IV-PCA) with sufentanil on an as-needed basis without a basal dose. The primary outcome is perceived pain intensity as measured by visual analog pain score. Secondary outcomes include sufentanil consumption, time to first use of IV-PCA, rescue analgesics consumption, and the presence of adverse effects. Findings of this interventional trial will provide novel evidence supporting the superior effect of cocktail analgesic injection during surgery.

**Trial registration number::**

ChiCTR-IPR-17013094.

## Introduction

1

Patients undergone major spine surgery frequently experience severe pain after operation, lasting for more than 3 days.^[1]^ The underlying causes include direct surgical trauma^[2]^ and activation of multiple cellular targets pertinent to nociceptive, and inflammatory pathways.^[3]^ Peripheral and central sensitization further aggravates postoperative pain. Postoperative pain reduces patients’ satisfaction and substantially affects recovery, increases postoperative morbidities, and prolongs the length of hospital stay.^[4]^

Adequate postoperative pain management is essential to improve functional outcome, accelerate early ambulation, shorten the duration of hospital stay, and prevent subsequent development of chronic postsurgical pain. Different postoperative analgesics are available in various forms of administrative routes. Mechanisms contributing to postoperative pain in spine surgery are multifactorial. In this connection, single analgesic may be inadequate to achieve desirable outcomes. Compared with conventional analgesia, multimodal analgesia has recently gained popularity. This therapeutic approach combines different analgesics with multiple routes of administration to better optimize pain relief and minimize undesirable side effects and complications.^[5]^ While epidural and intravenous routes of drug administration may achieve analgesia,^[6–8]^ these costly procedures demand specialized skills and may confer nausea, vomiting, pruritus and urinary retention, respiratory depression, and neuraxial hematoma.^[9–11]^ In contrary, administration of local wound injection surrounding incision does not require highly trained personnel. This localized injection also facilitates drug delivery to the area of surgical wound and minimize systemic exposure.^[12–14]^ We propose a novel multimodal analgesic regimen containing several medications, designated cocktail analgesics, which are injected surrounding the surgical incision perioperatively. This study aims to evaluate the efficacy of cocktail analgesics for postoperative pain management amongst patients having 2-levels underwent lumbar spinal fusion surgery. We will determine if cocktail analgesic injection would provide satisfactory postoperative analgesia.

## Methods

2

### Study design

2.1

This is a single-center, prospective, double-blinded, randomized controlled trial. The protocol will be performed in accordance with the Declaration of Helsinki and was approved by the Ethics Committee of Peking Union Medical College Hospital. Written informed consent will be obtained from each patient before enrollment. This trial is registered with the Chinese Clinical Trial Registry (ChiCTR-IPR-17013094). An overview of the trial design is shown in Figure 1.

**Figure 1 F1:**
[figure not shown]
Trial flow diagram of the study.

### Study center

2.2

Our center is a tertiary referral hospital for spine surgery with the necessary types and volume of clinical cases required for this study. The research team comprises a chief spine surgeon and a team of experienced surgeons, nurses and allied health staff.

### Participants

2.3

Patients on the lumbar spinal fusions waiting list at Peking Union Medical College Hospital (PUMCH) will be invited to participate in this study. After initial screening, potentially eligible patients will be given a plain Chinese statement detailing the nature of the study and the commitment required. A trained researcher will obtain informed consent from eligible candidates who are willing to participate. Identified participants will be approached for inclusion in the study according to predefined inclusion and exclusion criteria.

### Inclusion criteria

2.4

(1)Age between 18 and 70 years.(2)On the surgical waiting list for primary 2-level lumbar spinal fusion surgery diagnosed with lumbar spinal stenosis or lumbar disc herniation.(3)American Society of Anesthesiologists physical status I∼II.(4)Understand and comply with the study protocol.

### Exclusion criteria

2.5

(1)History of hypersensitivity to parecoxib, ropivacaine, diprospan, fentanyl, or sulfonamide.(2)Perioperative period of coronary artery bypass surgery.(3)Pregnant, lactating, or probably pregnant.(4)Revision surgery or surgery for neoplastic disease.(5)Inability to provide informed consent due to mental incompetence

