### Cocktail anesthetic preparation

2.9

Cocktail solution will contain ropivacaine 1%, 200 mg (20 ml), parecoxib 40 mg, betamethasone 7 mg (1 ml), mixed with normal saline into a total volume of 50 ml.

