### Cocktail analgesic injection group (cocktail group)

2.10

In the cocktail group, cocktail analgesics will be injected surrounding the deep fascia and the muscular layer in the surgical wound before final wound closure. A total of 35 ml trial solution will be used. Postoperative analgesia will be provided by intravenous patient-controlled analgesia (IV-PCA) delivering sufentanil 2 μg in each bolus, with a 15-minute lockout interval. No basal infusion will be used. PCA pump will be removed in 48 hours after surgery.

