### Sterile saline injection group (control group)

2.11

In the control group, an equal volume of saline (35 ml) will be injected to the deep fascia and the muscular layer in the surgical wound in the same fashion as the cocktail group. IV-PCA will be provided in the same mode.

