### Rescue analgesia

2.13

Patients who require an additional analgesic after PCA removal will be provided with tramadol 50 mg intramuscularly route each time. Usually, the need for supplementary treatment with systemic opioids is a reliable indicator when concerned about postoperative pain control. Having considered that the use of strong or long-term rescue analgesia in both groups may reduce pain too much and “washed out” any differences between the 2 groups. In this study, we use tramadol hydrochloride injection for rescue analgesia, which is a mid-intensity opioid analgesic that will facilitate observing the differences in pain control between groups. The frequency and total dosage during the first 3 postoperative days will be recorded.

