### Criteria for discontinuation

2.19

Every effort will be made to retain patients in the trial and to minimize withdrawals. However, the trial will be discontinued on condition that any SAEs happen. Additionally, patients may request to be withdrawn from this study at any time without any reason. Intention to treat and “as treated” analyses will be performed.

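### The hypersensitivity exclusion names fentanyl, which the article does not say is given, but not sufentanil, provided to all patients by IV-PCA, nor tramadol, the conditional rescue drug

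*Protocol article*

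**What the plan says.** Section 2.5 of the protocol article gives five exclusion criteria. The first is the only one about drug reactions: "History of hypersensitivity to parecoxib, ropivacaine, diprospan, fentanyl, or sulfonamide". It is a closed list, with no general wording such as any study drug.

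The treatments are named elsewhere:

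- **Cocktail (section 2.9):** ropivacaine, parecoxib and a steroid, written as "betamethasone 7 mg (1 ml", made up with saline.
- **PCA, cocktail group (section 2.10):** "Postoperative analgesia will be provided by intravenous patient-controlled analgesia (IV-PCA) delivering sufentanil 2 μg in each bolus, with a 15-minute lockout interval".
- **PCA, control group (section 2.11):** "IV-PCA will be provided in the same mode".
- **PCA, both groups (abstract, Methods):** "All patients will routinely receive postoperative intravenous patient-controlled analgesia (IV-PCA) with sufentanil on an as-needed basis without a basal dose".
- **Rescue (section 2.13):** "we use tramadol hydrochloride injection for rescue analgesia", for patients who need more analgesia once the PCA has been removed.

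Section 2.12 says that surgery is under general anaesthesia but names no anaesthetic agent.

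**The concern.** A hypersensitivity exclusion is normally read as protecting participants from drugs they will meet in the trial. Here the opioid in the list and the opioids in the treatment sections are different drugs by name. A screener who applies criterion (1) as printed would turn away a patient with a fentanyl reaction and find no reason in the list to turn away one with a sufentanil reaction, although all 36 planned patients are provided with sufentanil.

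Two things are at stake. The first is safety: the eligibility rule does not cover the trial's routine PCA drug. The second is outcome data. Sections 2.16.1 and 2.16.2 take sufentanil consumption and time to first use of IV-PCA as secondary outcomes over the first 48 hours. For a randomised patient who cannot use the PCA, low consumption or no first use would not reflect pain control.

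**Working it through.** No formula applies. The check sets the drugs named as given against the entries in criterion (1). Fluids and oxygen (section 2.12) are left out.

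| Drug named as given | Where | To whom | In criterion (1)? |
|---|---|---|---|
| Ropivacaine | 2.9 | Cocktail group | Yes |
| Parecoxib | 2.9 | Cocktail group | Yes |
| Betamethasone | 2.9 | Cocktail group | Not under that name |
| Sufentanil | Abstract, 2.10, 2.11, 2.16.1 | All patients, as needed | No |
| Tramadol | 2.13, 2.16.3 | Only those needing rescue after PCA removal | No |

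By name, 2 of the 5 drugs are listed and 2 are not. The fifth, betamethasone, is listed only if diprospan is another name for it, and the article never links the two.

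The same check from the list's side:

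| Entry in criterion (1) | Named elsewhere as given? |
|---|---|
| Parecoxib | Yes |
| Ropivacaine | Yes |
| Diprospan | Not under that name |
| Fentanyl | No; the word occurs only here |
| Sulfonamide | No; the word occurs only here |

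Next, does any other criterion close the gap? The other four exclusions concern coronary bypass surgery, pregnancy or lactation, revision or tumour surgery, and capacity to consent. The four inclusion criteria concern age, the planned operation and diagnosis, ASA status, and understanding of and compliance with the protocol. None mentions drug allergy.

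So, on the text, a known sufentanil reaction meets no exclusion criterion, and the same is true of tramadol. The sufentanil gap is the more important. The PCA is provided to everyone and two secondary outcomes depend on it, whereas tramadol reaches only patients who ask for more after the pump is removed.

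**The case against.** The strongest reply is that the list was never meant to match the treatments one for one. Sulfonamide is also listed and is given to nobody, so the fact that fentanyl appears nowhere else does not prove an error. Fentanyl may be a slip for sufentanil, a stand-in for the opioid class, or an anaesthetic agent that this article, as a condensed account, does not name. Under the first two readings sufentanil was meant to be covered and only the wording needs repair. This stands, and it is why the point does not call the fentanyl entry wrong. It does not remove the gap. The article states none of these readings, and under the third sufentanil is still uncovered.

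It can also be said that the compliance criterion in section 2.4, or routine allergy checks, would catch such a patient. They might in practice. But the compliance criterion does not mention allergy, and a check made after enrolment would leave a randomised patient who cannot follow the regimen.

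Some stronger readings are tempting, and the documents do not support them:

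- **One preventable reaction would end the trial.** Section 2.19 does say that "the trial will be discontinued on condition that any SAEs happen". That rule covers a serious event from any cause, so its breadth is a separate matter and adds no weight here.
- **The primary outcome is compromised.** Five of the six VAS times (6, 12, 24, 36 and 48 hours) fall while the PCA is in place. But the article does not say how a patient unable to use it would be managed, so no effect on pain scores can be derived.
- **The arms would be biased.** Allocation is random at 1:1, and nothing suggests that such patients would gather in one arm.
- **The steroid is uncovered.** Two names are used for what may be one drug. That is an inconsistency in naming, not a shown gap in coverage.
- **Every participant is exposed to tramadol.** Its use is conditional.

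**Conclusion.** The point holds as a mismatch between a stated eligibility rule and the stated treatments. Criterion (1) names one opioid that the article does not say is given and omits both opioids that it does name. The main consequence is that a patient with known sufentanil hypersensitivity is not excluded by the criteria as printed.

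Its size is limited. The article gives no hypersensitivity rates, so no expected number of patients can be stated. For scale only, one such patient would be 1/18 = 5.6% of an arm. The outcomes directly touched are secondary: sufentanil consumption and time to first PCA use, and, conditionally, rescue consumption. No error in power or in the primary analysis follows.

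The conclusion rests on two assumptions: that the list is closed, as printed, and that the full protocol does not define fentanyl more widely. If the full protocol already settles this, the article needs only to be brought into line with it. Because the rule governs who enters the trial, it is worth correcting even though such patients may be few.

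**What to change.** Reconcile criterion (1) in section 2.5 with the drugs named in sections 2.9, 2.10, 2.11 and 2.13. In doing so:

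1. State whether fentanyl is meant as sufentanil, as the opioid class, or as an anaesthetic agent used in the trial, and word the entry to match.
2. Record a decision on sufentanil and tramadol, so that their absence from the list is either corrected or explained.
3. Use one name for the steroid throughout, or state how diprospan and betamethasone relate.

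Which drugs belong in the list is for the clinical team to decide; this review does not propose its content.

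The cost is a one-line change to the eligibility text, with the matching update to screening documents. Sample size, randomisation and analysis are unaffected. The documents give no rate from which to put a figure on any effect on recruitment.

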### Randomization

2.6

Random assignment will be performed before surgery using a computer-generated, block random-allocation sequence with a 1:1 ratio. Allocation concealment will be achieved using opaque sequentially numbered sealed envelopes. The research staff will record the patients’ details.

### Blinding

2.7

The cocktail analgesic or equivalent volume of saline is prepared by pharmacy independent to the trial in an aseptic fashion. Both the attending surgeon and the patients will be blinded to the group allocation. Data will be collected by research staff blinded to group allocation. Upon completion of the study, a biostatistician blinded to group allocation will analyze outcome data.

### Interventions

2.8

All patients will be randomized using a computer-generated list to 1 of 2 groups, 1 of which will receive subcutaneous injection of cocktail analgesic at final wound closure during surgery (cocktail group). Control group patients will receive equivalent volume of saline. The same surgeon will perform all operations. All patients will undergo 2-level posterior lumbar spinal fusions with pedicle screws and rod fixation.

### Cocktail anesthetic preparation

2.9

Cocktail solution will contain ropivacaine 1%, 200 mg (20 ml), parecoxib 40 mg, betamethasone 7 mg (1 ml), mixed with normal saline into a total volume of 50 ml.

### Cocktail analgesic injection group (cocktail group)

2.10

In the cocktail group, cocktail analgesics will be injected surrounding the deep fascia and the muscular layer in the surgical wound before final wound closure. A total of 35 ml trial solution will be used. Postoperative analgesia will be provided by intravenous patient-controlled analgesia (IV-PCA) delivering sufentanil 2 μg in each bolus, with a 15-minute lockout interval. No basal infusion will be used. PCA pump will be removed in 48 hours after surgery.

### Sterile saline injection group (control group)

2.11

In the control group, an equal volume of saline (35 ml) will be injected to the deep fascia and the muscular layer in the surgical wound in the same fashion as the cocktail group. IV-PCA will be provided in the same mode.

### Perioperative management

2.12

Surgery will be performed under general anesthesia with standardized fashion. A standardized intraoperative strategy for fluid management will be applied which consists of 0.9% saline at 5 ml/kg/h and hydroxyethyl starch colloid at 7.5 ml/kg/h. At the end of the surgery, the PCA pump will be started on without a basal dosage, which will be removed 48 hours later. After surgery, patients will be taken to the recovery room and monitored according to standard hospital policy. Patients will be educated with the use of the PCA device and discharged to the ward, once recovery room discharge criteria have been met. Patients will receive supplemental oxygen via nasal cannula at 2 l/min for 24 hours. The time to first mobilization will be recorded and the patient will continue to be monitored until discharge. Any serious adverse events (SAEs) will prompt follow up. Patients will be followed up routinely at 4 weeks after discharge by the spine specialist. Symptoms of nerve damage will be actively sought at this consultation.

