#### Time to first use of IV-PCA

2.16.2

The time to first use of IV-PCA and proportion of the patients during the first 48 hours postoperatively will be recorded.

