### Sample size

2.17

The sample size calculation was based on the following parameters:

(1)alpha value = 0.05, 2-sided;(2)power = 80%.

The minimal clinical significance in VAS pain score was defined as the mean difference between current and preceding scores when the subject reported “a little worse” or “a little better” pain. Our pilot study shows that VAS pain scores 72 hours after lumbar spinal fusion surgery were reported to be 2.1 ± 1.6 in patients receiving cocktail analgesic injection and 5.6 ± 1.7 in patients without. Based on these findings, we hypothesized that VAS pain score 72 hours after surgery will be 2.5 for the cocktail group and 5.0 for the control group, with a standard deviation set at 2.5 and a ratio of patients in the cocktail to the control group of 1:1. Calculations showed that a sample size of 14 patients per group to detect a difference in VAS pain score between the 2 groups after treatment. Assuming a 20% dropout rate, 18 patients per group, or a total of 36 patients, are required.

It is anticipated that recruitment for this study will take 6 months to complete, using 1 surgeon to reduce surgical variability. Data collection for each patient will occur during the first 72 hours postoperatively and at a routine 4-week follow-up appointment. No further follow up will be routinely arranged. Any patients requiring specific follow up will have this arranged on an individual basis.

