### Data analysis

2.21

Data distribution will be tested for normality using the Shapiro–Wilk test. Skewed data will be corrected by logit-transformation as appropriate and subsequently examined using parametric test in order to preserve statistical power. For data set that cannot be normalized by logit-transformation, nonparametric test will be applied. Group comparison will be done by Student *t* test and Mann–Whitney *U* test for parametric and nonparametric data, respectively. Pearson Chi-square will be used for categorical variables. In strata where the expected counts are less than 5, Fisher exact test will be used. Univariate logistic regression and simple linear regression will be performed to determine potential predictors associated with binary outcomes and continuous outcomes, respectively. For predictors significantly associated with the outcomes of interest (*P* < .1), they will be further examined for co-linearity using Chi-square test, 0-order Pearson product-moment correlation, or Student *t* test as appropriate. For continuous variables with variable inflation factor greater or equal to 10, only 1 variable will be kept for subsequent analysis. After removing redundant co-variates, multivariate regression models will be built. The goodness-of-fit of the final models will be determined by the Hosmer–Lemeshow test (logistic regression) or *R*^2^ (multiple linear regression), respectively. For time-to-event outcomes, multivariate Cox proportional hazard regression models will be built. The cumulative probability of an outcome event over time will be presented in form of Kaplan–Meier curves.

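### PCA teaching is placed at recovery-room discharge, after the demand-only pump has started, so time to first use of IV-PCA may partly record when teaching happened

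*Protocol article*

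**What the plan says.** All references are to the protocol article.

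- **Pump start (Perioperative management):** "At the end of the surgery, the PCA pump will be started on without a basal dosage, which will be removed 48 hours later". The section on the cocktail group confirms boluses only, with a 15-minute lockout and no basal infusion. The control group section says "IV-PCA will be provided in the same mode".
- **Teaching (same section, after transfer to the recovery room):** "Patients will be educated with the use of the PCA device and discharged to the ward, once recovery room discharge criteria have been met". No earlier instruction is described anywhere in the article.
- **Outcome (Time to first use of IV-PCA):** "The time to first use of IV-PCA and proportion of the patients during the first 48 hours postoperatively will be recorded". The window is 48 hours after surgery. The instant at which the clock starts is not given.
- **Analysis (Data analysis):** "For time-to-event outcomes, multivariate Cox proportional hazard regression models will be built", with Kaplan–Meier curves.

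**The concern.** With a demand-only pump, first use requires both pain and knowledge of how to press. The plan opens the window at or near the end of surgery and places the teaching inside it. For a patient in pain before teaching, the recorded time is then set by recovery-room logistics. For a patient whose pain comes later, the recorded time is the true one.

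If the injection works, early pain is more common in the control arm, so the limit falls mainly on that arm. Time to first demand is also the listed outcome closest to the duration of action of a wound injection. What is at stake is the reported size of that effect and, with 18 patients per arm, some of the power to see it.

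**Working it through.** The article gives no figure for this outcome that could be reproduced. It has no expected time to first demand, no recovery-room duration and no teaching time. **All times below are assumptions.** Taken from the document: 18 per group, "alpha value = 0.05, 2-sided", and IV-PCA delivered alike in both arms.

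**Model.** Let D be the time at which a patient would first demand a bolus and T the time of teaching, both from end of surgery. A patient who needs a bolus before teaching presses as soon as taught, so the recorded time is max(D, T). With exponential D of median m and a fixed T:

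- share recorded at the floor = 1 − 2^(−T/m)
- recorded median = max(m, T)

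With the same T in both arms, the recorded median difference is max(m_cocktail, T) − max(m_control, T). This can never exceed m_cocktail − m_control when the cocktail median is the longer.

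**Early demand: medians 0.5 h (control) and 1.5 h (cocktail).** Shares at T = 1 h: 1 − 2^(−2) = 75% of control and 1 − 2^(−0.667) = 37% of cocktail patients. At T = 2 h: 1 − 2^(−4) = 94% and 1 − 2^(−1.333) = 60%. Power is from a simulated log-rank test, 18 per arm.

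| Teaching time | Median difference | Power |
|---|---|---|
| none (no floor) | 1.5 − 0.5 = 1.0 h | about 88% |
| 1 h, fixed | 1.5 − 1.0 = 0.5 h | about 87% |
| 2 h, fixed | 2.0 − 2.0 = 0 h | about 80% |
| varies 0.5–1.5 h, independent of arm | about 0.4 h | about 82% |
| varies 1–3 h, independent of arm | about 0.4 h | about 55% |

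A fixed floor mostly damages the size of effect. Variation in teaching time also costs power, because it adds noise unrelated to pain.

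**Later demand.** Here teaching times vary modestly around the stated value and the test is Mann–Whitney.

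| Medians (control, cocktail) | Teaching | Median difference, true → recorded | Power, true → recorded |
|---|---|---|---|
| 1 and 3 h | 0.5 h | 2.0 → 2.0 h | 77% → 76% |
| 1 and 3 h | 1 h | 2.0 → 1.7 h | 76% → 75% |
| 1 and 3 h | 2 h | 2.0 → 0.9 h | 75% → 64% |
| 2 and 6 h | 1 h | 4.0 → 4.0 h | 77% → 76% |
| 4 and 8 h | 1 h | 4.0 → 4.0 h | 41% → 41% |

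**Teaching time that differs by arm (medians 1 and 3 h).** With teaching at 2 h in control and 1 h in cocktail, the median difference falls to 0.8 h and power to 19%. With the reverse, the mean difference rises from 2.9 to 3.0 h and the rejection rate from 76% to 99%. The direction is therefore fixed only when teaching time is similar in both arms.

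**Sufentanil.** Boluses are 2 μg with a 15-minute lockout, so one hour without use removes at most 4 × 2 = 8 μg. The pump's 48-hour ceiling is 48 × 4 × 2 = 384 μg, so 8 μg is about 2% of it, and later demands may make some of it up.

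**The case against.** **The article is condensed.** Time origin, time stamps and earlier patient instruction commonly sit in a full protocol or analysis plan that is not shown. This stands for the missing origin taken alone, which would not be a point. It does not dispose of the timing of teaching, which the article states and places inside the outcome's window.

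**The sentence on teaching can be read more loosely.** The condition about discharge criteria might govern discharge alone, with teaching somewhat earlier in the recovery-room stay. That is possible, and instruction before surgery is not expressly excluded. Either way, the only teaching described comes after the pump is running.

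**Stronger readings are not supported.** A reader might infer that the clock runs from pump start, that the patient is still anaesthetised then, and that nobody is taught before recovery-room discharge. The article says "Surgery will be performed under general anesthesia with standardized fashion" but does not describe the patient's state when the pump is started, and it states neither of the other two. A reader might also infer that the difference between groups is certain to shrink. That needs teaching late enough to bind, and similar in both arms. Similarity is plausible given "Both the attending surgeon and the patients will be blinded to the group allocation" and the common PCA mode, but pain could itself affect time to recovery-room discharge.

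**The effect may be small.** This stands. With demand medians of 2 h or more in control and teaching at 1 h, nothing material changes. Large losses need early demand, late teaching or variable teaching. The figures also concern medians and rank-type tests; no effect on the planned Cox hazard ratio was computed.

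**Conclusion.** The point holds in a limited form. As written, a secondary outcome that depends on the patient knowing how to press may partly record when teaching happened. With similar teaching times in both arms this cannot widen the contrast and probably attenuates it. The attenuation of the median difference runs from nil to most of it (all of it in the most extreme case tried). Where within that range the trial would fall depends on demand and teaching times that the document does not give.

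A reader might extend this to the main result or to opioid use. Neither follows: the primary VAS outcome is not affected by this route, and an effect on the 48-hour sufentanil difference is not shown. The case for acting rests on the low cost of the repair, not on a demonstrated large bias.

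**What to change.** Reconcile the sections on perioperative management and on time to first use of IV-PCA:

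1. Complete PCA instruction before the measurement window opens, for example at the preoperative visit, with a reminder on waking.
2. State end of surgery as time zero for the main analysis.
3. Record the clock time of instruction and the clock time at which the patient is first awake and able to press.
4. Report time from first being able to press as a sensitivity analysis only. That moment comes after randomisation and may itself depend on treatment, and starting the clock there does not remove a floor set by late teaching.

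The cost is a few minutes at an existing visit and one or two time stamps. No dose, lockout or rescue rule changes.
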